## Response evaluation for non-target lesions

|                             |                                                                                                                                                                                                                                       |
|-----------------------------|---------------------------------------------------------------------------------------------------------------------------------------------------------------------------------------------------------------------------------------|
| CR
(Complete response)   | When all non-lymph node lesions disappear, all tumor markers fall within the upper limit of the facility's normal reference values, and the short diameters of all lymph node target lesions become < 10 mm.                          |
| Non-CR/non-PD               | When $\geq 1$ non-lymph node lesions do not disappear, or the short diameters of $\geq 1$ lymph node non-target lesions are $\geq 10$ mm, or $\geq 1$ tumor marker exceeds the upper limit of the facility's normal reference values. |
| PD
(Progressive disease) | "Obvious progression" of non-target lesions (including incidence of new lesions) (see the comments below the table for the definition of obvious progression).                                                                        |
| NE
(Not evaluable)       | When tests cannot be done for any reason, or when a lesion cannot be determined to be any of CR, non-CR/non-PD, or PD.                                                                                                                |

## Obvious progression

- Cases with non-measurable lesions will be considered to show "obvious progression" when it is determined that the benefits of discontinuing the treatment are greater than those of continuing the treatment because of a notable exacerbation of non-target lesions, even if the target lesions are PR or SD.
- In cases with only non-measurable lesions, for example, when lesion volume is used as a guide, an increase in the volume of non-measurable lesions of 73% will be considered to be "obvious progression".

## Incidence of new lesion(s)

- When a lesion that did not exist at baseline is observed after the initiation of treatment, this will be considered a "new lesion". However, it is also necessary to confirm that the "new lesion" is not observed due to a difference in the scan method or imaging modality compared with that used for baseline evaluation or a clinical condition other than a tumor. For example, a cystic lesion occurring in a focus caused by necrosis of liver metastasis will not be considered to be a "new lesion". Lesions that are newly found on examination of regions that were not regarded to be essential for examination at baseline will be considered to be new lesions. When a lesion that existed at baseline disappears and then appears again, such a lesion will be considered to be "PD" if this reappearance occurred after the overall response became CR; however, if other lesions are remaining, the lesion will not be considered to be a "new lesion" or "PD" because of the reappearance alone, but its tumor diameter will be added to the sum of diameters if the lesion is a target lesion. If the lesion is a non-target lesion, it will be considered to be "non-CR/non-PD" unless the lesion corresponds to "obvious progression".
- When a lesion may a new lesion but this cannot be confirmed, the lesion will not immediately be recorded as a new lesion, but imaging examination will be conducted after a clinically appropriate

interval. If the lesion is determined to be a new lesion by the imaging re-examination, the date of imaging examination when a new lesion was suspected shall be used as the date of incidence for the new lesion.

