## (5) Time point response

The time point response will be determined at each image evaluation time point in accordance with the criteria specified in the table below based on a combination of the response of target lesions, response of non-target lesion, and incidence of new lesions.

When there are no non-target lesions at baseline, the overall response will be determined based on the response of the target lesion and incidence of new lesions, and when there are no target lesions at baseline, the overall response will be determined based on the response of non-target lesions and incidence of new lesions in accordance with the criteria specified in the table below.

Determination criteria for time point response (when target lesions are present).

| Response of target lesion | Response of non-target lesion | Incidence of new lesion | Overall response |
|---------------------------|-------------------------------|-------------------------|------------------|
| CR                        | CR                            | No                      | CR               |
| CR                        | Non-CR/Non-PD                 | No                      | PR               |
| CR                        | Not evaluated                 | No                      | PR               |
| PR                        | Non-PD or not fully evaluated | No                      | PR               |
| SD                        | Non-PD or not fully evaluated | No                      | SD               |
| Not fully evaluated       | Non-PD                        | No                      | NE               |
| PD                        | Any                           | Yes or No               | PD               |
| Any                       | PD                            | Yes or No               | PD               |
| Any                       | Any                           | Yes                     | PD               |

Determination criteria of time point response (when target lesions are absent).

| Response of non-target lesions | Incidence of new lesions | Overall response |
|--------------------------------|--------------------------|------------------|
| CR                             | No                       | CR               |
| Non-CR/Non-PD                  | No                       | Non-CR/non-PD    |
| Not fully evaluated            | No                       | NE               |

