### 3.9 Definition of outcome measures in this study

#### (1) Clinical benefit rate (CBR)

The clinical benefit rate is defined as the rate of patients who are not determined to have experienced disease "progression" for 6 months from the initiation of treatment.

"Patients who are not determined as 'progression' for 6 months" means patients whose time point response {3.8 (5) Determination criteria of time point response} based on diagnostic imaging implemented at 3 and 6 months from the initiation of treatment is CR, PR, or SD at any time point, and for whom no clinical progression was observed for 6 months from the initiation of treatment {3.8 (7) Clinical progression}.

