#### (2) Progression-free survival (PFS)

A period of time from the registration day to either of the day when progress was determined or the day of death from all causes (whichever is earlier). The following criteria are specified for the determination of PFS.

- ① "Progression" includes both progression in the determination of the total effect {3.8 (5) Determination criteria of time point response} and progression of the original disease based on a method other than diagnostic imaging {3.8 (7) Clinical progression}.

When the progression is determined based on diagnostic imaging, the date for which progression is recorded will be the day of the examination. In the case of clinical progression, the date of clinical determination will be recorded as the date of progression.

- ② In survival cases that are not determined to have experienced progression, the most recent day on which no progression is confirmed will be the recorded date for PFS.
- ③ When the diagnosis of progression is based on diagnostic imaging, the date recorded will be the "examination day" of the diagnostic imaging that provided "certain diagnosis" but not the day of examination where the progression was suspected as "suspicious on image". When the progression is determined clinically but is not based on diagnostic imaging, the date recorded for progression will be the day when the progression was determined.
- ④ The development of secondary cancer(s), e.g. heterochronic double cancer or heterochronic multiple cancer, will not be considered an event and will not be recorded as such, but will be considered to be PFS until another event is observed.
- ⑤ When treatment is discontinued due to the characteristics of or rejection by the patient and other treatment is implemented as an after-treatment, such cases will be handled in the same manner as the above for recording events and the endpoint, and will not be recorded at the time of discontinuation of treatment or the date of the initiation of after-treatment.

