#### (3) Overall survival (OS)

The period of time from the registration day to the day of death from all causes. The final confirmation day of survival in survival cases will be the recorded date.

For cases that are lost to follow-up, the last date when survival of the patient was confirmed before becoming lost to follow-up will be the recorded date.

(4) Time to treatment failure (TTF)

A period of time from the registration day to either of the day when progress was determined, the day of death from all causes, or the day of discontinuation of the protocol treatment (whichever is earlier).

- ① The day of discontinuation of the protocol treatment is the day when the discontinuation will be determined.
- ② "Progression" includes both progression in determination of the total effect {3.8 (5) Determination criteria of time point response} and progression of the original disease based on methods other than diagnostic imaging {3.8 (7) Clinical progression}.  
When the progression is determined based on diagnostic imaging, the date recorded for progression will be the day of the examination. In the case of clinical progression, the date recorded for progression will be the day of clinical determination.
- ③ When the diagnosis of progression is based on diagnostic imaging, the date recorded for the event will be the examination day when the diagnostic imaging was performed that provided certain diagnosis, but not the day of examination where progression was suspected as "suspicious on image". When the progression is determined clinically but not based on diagnostic imaging, the date recorded for progression will be the day when the progression was determined.
- ④ When the protocol treatment is continuously implemented and there is no progression, the treatment will be discontinued on the final confirmed day of survival (the final confirmed day of PFS).

(5) Time to chemotherapy (TTC)

The period of time from the registration day to the day of first administration of chemotherapeutic drug

- ① For cases where mortality occurred before the initiation of chemotherapy, the date of death will be the recorded date.
- ② For cases that are lost to follow-up and in which implementation of chemotherapy is not confirmable, the last date when survival of the patient was confirmed before becoming lost to follow-up will be the recorded date.

(6) Response rate (RR)

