- D) Presence or absence and reasons for implementation of concomitantly used therapies (surgical therapy for breast cancer focus, radiotherapy for breast cancer focus, molecularly-targeted drugs other than mTOR inhibitors, chemotherapy, immunotherapy, other drugs recognized to have antitumor activity against breast cancer) for the past 3 months

(7) Survey plan at 6 months or later after the initiation of protocol treatment or after discontinuation of the protocol treatment

① Timing of survey

- A) Every year from 6 months after the initiation of the protocol treatment when the protocol treatment is ongoing at the time of 6 months after the initiation of the protocol treatment
- B) Every year from the day of discontinuation of the protocol treatment when the protocol treatment is discontinued at the time of 6 months after the initiation of the protocol treatment

② Contents of survey

- A) Continuation state of protocol treatment: Presence or absence of continuation of the protocol treatment. If it is discontinued, the date and reasons for the discontinuation {only for subjects corresponding to the criteria specified in 5.4 (7) ①-A)}.
- B) Survey of progression: Presence or absence of progression defined in 3.9 (2). When progression was observed, the date when the progression occurred was determined (not required for a subject whose progression is already reported.)

- C) Survey of after-treatment: Presence or absence of implementation of chemotherapy. If chemotherapy is implemented, the date and type of chemotherapy.
- D) Survey of prognosis: The final confirmed day of survival. In case of death, the date and cause of death.

(8) Discontinuation of survey

When a case meets one of the following criteria, the survey will be discontinued.

- ① When it is determined that continuation of the rest of the survey is not possible due to changing hospital or other reasons
- ② Withdrawal of consent
- ③ Death
- ④ When it becomes clear that the eligibility criteria are not satisfied
- ⑤ Other reasons, when it is determined that continuation of the study as a subject is not possible

---

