### 7.3 Sample size determination

This study is an observational study, in which therapy is selected based on the preferences of medical staff and patients. The study does not aim to compare different cohorts. To test the major study hypothesis, the threshold clinical benefit rate is set as 30%, and the expected clinical benefit rate is set as 50% in each cohort. Assuming the use of an accurate binomial test, it is estimated that the required number of cases is 43 under a condition of  $\alpha=0.05$  (one-tailed) and  $\beta=0.2$ . Assuming a dropout rate of about 10%, the target sample size estimated to be required for each cohort was set at 50. This study is an observational study, and cases will not always be evenly distributed to each cohort. However, it is needed to set the sample size corresponding to the 4 groups at a maximum [(4) Selection of drugs]. Therefore, a target case quantity of at least 200 was set. Meanwhile, registration will continue until all 4 groups achieve the target number of 50 cases per group within the time frame set for registration, even after a total registration number of 200 cases is achieved.

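### Sections 3.8 and 3.9 date a suspected, later confirmed new lesion to different scans, giving one patient two possible PFS and TTF event dates

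*Protocol*

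**What the plan says.** Four parts of the protocol bear on the date of imaging progression.

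- **3.8 (4), Incidence of new lesion(s).** A doubtful lesion is not recorded as new at once; imaging is repeated after an interval left to clinical judgment. If the repeat confirms it, "the date of imaging examination when a new lesion was suspected shall be used as the date of incidence for the new lesion".
- **3.8 (5), Time point response.** The response at each imaging time point is "based on a combination of the response of target lesions, response of non-target lesion, and incidence of new lesions". In both tables, a new lesion gives PD whatever the other components show.
- **3.9 (2), PFS, and 3.9 (4), TTF.** Under item 1 of 3.9 (2), progression "includes both progression in the determination of the total effect", with a reference to 3.8 (5). Item 2 of 3.9 (4) does the same for TTF. Item 3 of each section then dates imaging progression to the examination that gave a definite diagnosis: "but not the day of examination where the progression was suspected as" suspicious for PFS, and "but not the day of examination where progression was suspected as" suspicious for TTF.
- **3.9 (1), CBR.** A patient has clinical benefit if progression is not determined for 6 months. On imaging, this means that the 3.8 (5) assessment "based on diagnostic imaging implemented at 3 and 6 months from the initiation of treatment is CR, PR, or SD at any time point". In addition, clinical progression must be absent. The section gives no rule for a lesion that is doubtful at the 6-month scan.

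**The concern.** Sections 3.8 and 3.9 give opposite instructions for the same sequence of scans: a new lesion is suspected, then confirmed. One goes back to the scan of suspicion and the other expressly rejects it. PFS and TTF are secondary endpoints estimated by Kaplan-Meier, so their curves could mix two event definitions.

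The listed contents of the progress reports (5.7) include no separate date of first suspicion. If the rule is not settled before data are collected, the convention a site used may not be recoverable at analysis.

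There is also a question of consistency with the primary endpoint. CBR is classified through 3.8 (5), while PFS takes its date from 3.9 (2), so the two can disagree for one patient.

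**Working it through.** The core of the point is textual, so the passages are taken in order before any arithmetic.

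**Step 1. Do both rules reach the same event?** A confirmed new lesion is PD under 3.8 (5). Item 1 of 3.9 (2) and item 2 of 3.9 (4) take 3.8 (5) progression as the PFS and TTF event. So both rules apply to one event, and no sentence ranks them.

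**Step 2. A worked patient.** A new lesion is suspected on the 6-month scan and confirmed on a scan *d* months later. Times run from the start of treatment.

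| | Rule in 3.8 (4) | Item 3 of 3.9 (2) and 3.9 (4) |
|---|---|---|
| Date of progression for PFS and TTF | 6 months | 6 + *d* months |
| 6-month time point response | PD | not addressed |
| CBR through 3.8 (5) | failure | not addressed |

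PFS and TTF run from registration, which adds the same lead-in to both dates and leaves the difference at *d*. The CBR entry follows the requirement in 3.9 (1) that progression is not determined for 6 months.

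**Step 3. Which patients are affected?** For PFS and TTF, those whose first progression is a new lesion that was doubtful on one scan and confirmed on a later one. The back-dating sentence covers new lesions only. For doubtful growth of an existing lesion the protocol has just the 3.9 rule, so there is no conflict. For CBR, the case arises only when suspicion falls at or before month 6 and confirmation after it.

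**Step 4. Size for PFS and TTF, under assumptions.** The protocol gives neither the share of such progressions nor *d*. Assume a share of 20% and *d* of 1 to 3 months:

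mean shift among progressing patients = share × *d* = 0.20 × 1 = 0.2 months, to 0.20 × 3 = 0.6 months.

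**Step 5. Sensitivity for CBR, under assumptions.** First, the plan's own figure. In 7.3, "the threshold clinical benefit rate is set as 30%, and the expected clinical benefit rate is set as 50% in each cohort", with an exact binomial test, one-sided α = 0.05 and β = 0.2.

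- At n = 43, the smallest r with P(X ≥ r | 0.30) ≤ 0.05 is r = 19, with attained α = 0.0342.
- Power = P(X ≥ 19 | n = 43, 0.50) = 0.820, so the stated 43 is reproduced. It is the smallest n from which power stays at or above 80% for every larger n checked (up to 119). n = 39 and 41 also pass, but 40 and 42 do not.
- 43 / 0.9 = 47.8, which rounds up to 48; the protocol sets 50.

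Now suppose the true CBR is 50% if the later date is used for classification, and that dating to the scan of suspicion turns 0, 2, 5 or 10 points of it into failures. The power to exceed 30% is:

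| Points lost | n = 43 (r = 19) | n = 50 (r = 21) | n = 200 (r = 72) |
|---|---|---|---|
| 0 | 0.82 | 0.90 | 1.00 |
| 2 | 0.74 | 0.84 | 1.00 |
| 5 | 0.60 | 0.71 | 0.996 |
| 10 | 0.34 | 0.44 | 0.89 |

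Five points out of 50 means that 5/50 = 1 in 10 benefiting patients has a doubtful new lesion by the cut-off that is confirmed afterwards. Nothing in the protocol shows that this is realistic. The table shows only how sensitive a cohort-level test would be if the classification were applied differently.

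**The case against.** The best defence is that the endpoint-specific text governs. Section 3.9 (2) presents its items as the criteria for determining PFS and rejects the suspicious scan in terms. Section 3.8 opens as an evaluation of tumor reduction for the response rate. The later annual survey in 5.4 (7) collects progression as 3.9 (2) defines it, and the prognosis report in 5.7 (5) asks for a date of confirmation. Forms are also queried centrally (5.8, 25.1), so it is speculative that sites will in practice diverge.

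Much of this stands. It offers a workable reading for PFS and TTF and keeps the severity down. It does not remove the contradiction. CBR, PFS and TTF all cite 3.8 for progression, so 3.8 is not confined to the response rate. Nor can one date be called a lesion date and the other a progression date, since 3.8 (5) turns the lesion into PD.

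Four stronger readings are tempting but unsupported:

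- **Every equivocal progression is affected.** It is not; the back-dating sentence covers new lesions only.
- **CBR itself has two competing dates.** Section 3.9 (1) classifies rather than dates, refers to 3.8 (5), and does not import the date in 3.9 (2). What remains is its silence on a lesion confirmed after month 6, and the possible disagreement with PFS.
- **The study loses a known amount of power.** The frequencies are assumed. With the whole population of 200, power stays at or above 0.89 even with 10 points lost.
- **RECIST 1.1 settles the matter in favour of back-dating.** The protocol cites those criteria, but the source is not at hand, so the point does not rest on it.

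**Conclusion.** Wrong as written, of moderate severity, and mainly a matter for PFS and TTF. For a new lesion suspected on one scan and confirmed on a later one, 3.8 (4) and item 3 of 3.9 (2) and 3.9 (4) give different event dates, and the protocol does not say which applies. The difference per affected patient is the re-imaging interval.

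The aggregate effect cannot be derived from the document. The shift of 0.2 to 0.6 months rests on an assumed 20% share and an assumed interval of 1 to 3 months. The CBR power figures rest on assumed reclassification of 2 to 10 points. The link to CBR is indirect: the same patient can be a 6-month CBR failure through 3.8 (5) and have progression dated after the 6-month scan under 3.9. The sample size of 43 per cohort is reproduced and is not in dispute.

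**What to change.** Reconcile 3.8 (4) with item 3 of 3.9 (2) and 3.9 (4) so that one dating rule covers new lesions that are suspected and then confirmed. One way is to add an exception to item 3 in both places, saying that such lesions take the 3.8 date, and to leave item 3 unchanged for existing lesions. Rewriting item 3 throughout would go too far: it would extend back-dating to growth of existing lesions, where there is no conflict, and could date progression to a scan that did not meet the PD threshold. Adopting the 3.9 date for new lesions as well would be equally consistent, provided 3.8 (4) is changed to match.

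State in 3.9 (1) that the chosen rule also governs the 6-month CBR classification, including when confirmation comes after month 6. Have the progress report record the date that the rule requires; the prognosis item in 5.7 (5), which asks for a date of confirmation, would need aligning if the 3.8 date is kept.

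The cost is a few sentences and a note in the EDC instructions. If the 3.8 date is kept, PFS and TTF become slightly shorter.

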## (5) Time point response

The time point response will be determined at each image evaluation time point in accordance with the criteria specified in the table below based on a combination of the response of target lesions, response of non-target lesion, and incidence of new lesions.

When there are no non-target lesions at baseline, the overall response will be determined based on the response of the target lesion and incidence of new lesions, and when there are no target lesions at baseline, the overall response will be determined based on the response of non-target lesions and incidence of new lesions in accordance with the criteria specified in the table below.

Determination criteria for time point response (when target lesions are present).

| Response of target lesion | Response of non-target lesion | Incidence of new lesion | Overall response |
|---------------------------|-------------------------------|-------------------------|------------------|
| CR                        | CR                            | No                      | CR               |
| CR                        | Non-CR/Non-PD                 | No                      | PR               |
| CR                        | Not evaluated                 | No                      | PR               |
| PR                        | Non-PD or not fully evaluated | No                      | PR               |
| SD                        | Non-PD or not fully evaluated | No                      | SD               |
| Not fully evaluated       | Non-PD                        | No                      | NE               |
| PD                        | Any                           | Yes or No               | PD               |
| Any                       | PD                            | Yes or No               | PD               |
| Any                       | Any                           | Yes                     | PD               |

Determination criteria of time point response (when target lesions are absent).

| Response of non-target lesions | Incidence of new lesions | Overall response |
|--------------------------------|--------------------------|------------------|
| CR                             | No                       | CR               |
| Non-CR/Non-PD                  | No                       | Non-CR/non-PD    |
| Not fully evaluated            | No                       | NE               |
| Unequivocal PD                 | Yes or No                | PD               |
| Any                            | Yes                      | PD               |

(6) Best overall response

The best overall response will be considered in the order of CR > PR > SD > PD > NE. The overall evaluation at the best time point from the initiation of treatment through to the initiation of post-treatment will be considered to be the best overall response.

Meanwhile, determination of CR or PR in 4-week periods is not necessary in this study. When an overall response corresponds to the definition given for multiple categories, it will be categorized into the best-fitted category in the order of CR > PR > SD > PD > NE.

SD determination shall satisfy the SD standards after 6 weeks from the start of treatment. When an obvious deleterious change (exacerbation) of the disease is observed before the first effect determination, it will be considered to be PD when no imaging determination is implemented and NE when the determination was not conducted because of discontinuation of treatment due to adverse events or rejection by a subject.

(7) Clinical progression

Progression will be determined in accordance with the following criteria when using a method other than those defined in {3.8 (4) Determination of tumor reduction effect} or when progression in unmeasurable lesions is determined. However, progression will not immediately be determined even when a case corresponds to the following criteria but the judgment of a clinical investigator is prioritized. When image assessment is available, the image assessment will be prioritized.

- ① Confirmation of progression by ultrasound: When obvious progression such as emergence of new lesions, increased pleural effusion, etc. is observed by ultrasound.
- ② Confirmation of progression in bone lesion: When increased accumulation of bone is observed by scintigram or PET, or emergence of new lesions is observed in a bone lesion.
- ③ Exacerbation of subjective symptoms: When a clinical investigator determines there to have been progression, such as obvious exacerbation of bone pain in bone metastasis, obvious exacerbation of a sensation of dyspnea in lung metastasis, etc.

